## Abstract

**Background:**

Symptoms associated with pes planovalgus or flatfeet occur frequently, even though some people with a flatfoot deformity remain asymptomatic. Pes planovalgus is proposed to be associated with foot/ankle pain and poor function. Concurrently, the multifactorial weakness of the tibialis posterior muscle and its tendon can lead to a flattening of the longitudinal arch of the foot. Those affected can experience functional impairment and pain. Less severe cases at an early stage are eligible for non-surgical treatment and foot orthoses are considered to be the first line approach. Furthermore, strengthening of arch and ankle stabilising muscles are thought to contribute to active compensation of the deformity leading to stress relief of soft tissue structures. There is only limited evidence concerning the numerous therapy approaches, and so far, no data are available showing functional benefits that accompany these interventions.

**Methods:**

After clinical diagnosis and clarification of inclusion criteria (e.g., age 40–70, current complaint of foot and ankle pain more than three months, posterior tibial tendon dysfunction stage I & II, longitudinal arch flattening verified by radiography), sixty participants with posterior tibial tendon dysfunction associated complaints will be included in the study and will be randomly assigned to one of three different intervention groups: (i) foot orthoses only (FOO), (ii) foot orthoses and eccentric exercise (FOE), or (iii) sham foot orthoses only (FOS). Participants in the FOO and FOE groups will be allocated individualised foot orthoses, the latter combined with eccentric exercise for ankle stabilisation and strengthening of the tibialis posterior muscle. Participants in the FOS group will be allocated sham foot orthoses only. During the intervention period of 12 weeks, all participants will be encouraged to follow an educational program for dosed foot load management (e.g., to stop activity if they experience increasing pain). Functional impairment will be evaluated pre- and post-intervention by the Foot Function Index. Further outcome measures include the Pain Disability Index, Visual Analogue Scale for pain, SF-12, kinematic data from 3D-movement analysis and neuromuscular activity during level and downstairs walking. Measuring outcomes pre- and post-intervention will allow the calculation of intervention effects by 3×3 Analysis of Variance (ANOVA) with repeated measures.

**Discussion:**

The purpose of this randomised trial is to evaluate the therapeutic benefit of three different non-surgical treatment regimens in participants with posterior tibial tendon dysfunction and accompanying pes planovalgus. Furthermore, the analysis of changes in gait mechanics and neuromuscular control will contribute to an enhanced understanding of functional changes and eventually optimise conservative management strategies for these patients.

**Trial registration:**

ClinicalTrials.gov Protocol Registration System: ClinicalTrials.gov ID NCT01839669

## Background

The foot deformity pes planovalgus can cause symptoms or complaints, and may lead to dysfunction and functional limitation [1–3]. It can be an acquired entity where weakness of the plantarflexors and invertors of the foot (mainly the tibialis posterior muscle) cause a flexible or rigid flatfoot deformity [4, 5].

The posterior tibial tendon/muscle primarily serves as a dynamic stabiliser of the foot’s medial longitudinal arch [6]. Excessive stress can lead to tendinopathy of the posterior tibial tendon. This leads to posterior tibial tendon dysfunction (PTTD). Therefore, PTTD is most often accompanied by pes planovalgus foot deformity. Because of the mutual prevalence of both aspects, it is not clear if the muscle-tendon dysfunction is a result of the foot deformity [7, 8], or if it is causative for foot deformation [9, 10]. There is consensus that PTTD and pes planovalgus are closely connected [11–15].

Patients with PTTD and concomitant pes planovalgus report pain around the medial malleolus in the tibialis posterior muscle and its tendon. As the condition progresses, they can exhibit plantar hyperkeratosis in the talus area and lateral impingement at the fibula-calcaneal transition [2, 14, 15].

PTTD can be divided into four stages according to Johnson & Strom [2]. Stage I and II comprise a still flexible foot structure, which is considered to be eligible for non-surgical treatment. Stage III and IV contain already rigid longitudinal arch flattening with a tear of the spring ligament complex and talar valgus tilt in the ankle mortise [16]. Here, active compensation is not able to take place [17, 2].

As long as PTTD and the foot deformity demonstrate no symptoms, treatments are basically considered unnecessary [18]. If patients do have symptoms, however, a variety of therapy options may be administered: foot orthoses, ankle foot orthoses, stabilising tape, exercise (training therapy with, for example, eccentric exercise), pain medication and/or anti-inflammatory medication and patient education [11, 12, 15].

Optimisation of foot loading management by means of foot orthoses and adequate footwear is the most important aspect in therapy. Depending on the progression of the pathology, this can be progressively managed with over-the-counter non-individualised foot orthoses, then with individualised foot orthoses and finally with semi-rigid ankle foot orthoses [19]. These recommendations are published in clinical guidelines, but few high-quality studies have investigated their efficacy [11, 12].

Poor quality studies with a variety of uncontrolled interventions (foot orthoses, ankle foot orthoses, strengthening exercises, custom footwear, medication, ice, mega pulse and ultrasound – isolated or combinations) report possible benefits, but the lack of high quality, robust evidence does not allow conclusions for clinical practice [1, 20–22]. The only high-quality randomised controlled trial in patients with PTTD (and pes planovalgus) found that patients benefit most from a combination of foot orthoses and exercise after a 12-week intervention period [15].

Aside from clinical outcomes, functional impairments and their possible changes through interventions are not described in the literature on the basis of biomechanical measurements. Most often, static alignment measures of foot structure like ‘navicular drop’ as a composite for excessive pronation and/or longitudinal arch flattening are used to quantify flatfoot alignment [23, 24].

However, dynamic measurement is more valid because dynamic foot motion is not strongly associated with static alignment [23, 24]. Studies on foot kinematics between flat-arched feet and controls shows that foot function and arch flattening can be quantified with multi-segment foot models during weightbearing [25, 26]. Therefore, assessing foot structure during dynamic movement seems to be the current consensus [26–28].

Evaluations of neuromuscular function are very rare. A study investigating neuromuscular activity of the tibialis posterior muscle reports enhanced activity in flat-arched asymptomatic people during stance [29]. Tibialis posterior and peroneus longus muscle activity with the use of foot orthoses in flat-arched people changed [30], which is in contrast to O’Connor et al. who report that the tibialis posterior showed (at least in running motion) inconclusive activation patterns and no changes between different shoe conditions [31]. Another study showed reduced peroneus, lateral and medial gastrocnemius, and soleus muscle activity during early stance but enhanced tibialis anterior muscle activity in participants with asymptomatic flatfoot but with a history of musculoskeletal pain compared to controls [32]. This underlines the importance of readily available neuromuscular parameters describing gait function [33–35].

Some recent studies present sophisticated measurement approaches of dynamic foot function in pes planovalgus but to the authors’ knowledge, no study to date has evaluated dynamic foot function in patients suffering from acute complaints. Most studies use healthy controls or asymptomatic flatfooted subjects [36, 23, 37]. This makes it difficult to draw clear conclusions with regard to patients.

The aims of this study are therefore to: (i) analyse the efficacy of three different non-surgical therapy regimens in PTTD patients, and (ii) evaluate descriptively functional outcome with a comprehensive biomechanical measurement approach to learn more about functional changes in movement generation and its possible plasticity throughout the intervention.

## Methods

### Study design

The study design is a parallel-group randomised trial with three intervention groups receiving therapy regimens aimed at symptoms associated with pes planovalgus (Fig. 1). There will be an intervention phase of 12 weeks, which is a common therapy window for the associated symptoms of clinical problems like pes planovalgus [38]. Participants’ pain and functional impairment perception will be measured pre- and post-intervention (and in the middle of the intervention period). Biomechanical measurements (standardised laboratory study) before and after the intervention phase will accompany the protocol to evaluate possible functional changes induced by the therapy regimen.

**Fig. 1 Fig1:**
[figure not shown]
Study flow chart: randomisation of patients to one of three intervention groups: foot orthoses only FOO, foot orthoses and eccentric exercise FOE, sham foot orthoses only FOS

### Study population

A cohort of 60 participants will be recruited out of six state-wide foot surgery centres. To be included in the trial, participants will have to have: pes planovalgus, accompanying PTTD, associated foot pain; and a flexible foot structure, leading to eligibility for non-surgical treatment. Severe cases of flatfoot deformity indicating surgical correction (e.g., rigid foot structure and not being able to complete the test protocol due to severe pain or impaired physical function) will be excluded.

Specific inclusion criteria are similar to Kulig [15] and include:Age: 40–70 yearsCurrent complaint of foot and ankle pain that has lasted for three months or moreFlexible pes planovalgus deformity in the clinical assessmentPTTD of stage I and II according to Johnson & Strom [2]Pes planovalgus foot deformity with longitudinal arch flattening verified by radiograph [39]: Lateral view: lateral talo-first metatarsal angle ≠ 0° (break of axis): angle >10° according to Younger et al. [39], Anteroposterior view: anteroposterior talo-first metatarsal angle ≠ 0° (break of axis): angle >10° according to Younger et al. [39]No indication/not yet an indication for surgical treatment of foot deformity

Exclusion criteria are again similar to Kulig [38] and include:Rigid foot deformityPTTD of stage III and IV according to Johnson & Strom [2]Cardiac, neurological, peripheral vascular, or musculoskeletal pathologyAcute infection or alcohol addiction limiting participation in study protocolAcute use of local or systemic analgesicsAcute physical therapy, training therapy or physiotherapyAcute overuse or traumatic injury to the lower leg (excluding pes planovalgus associated pathology)Prior surgery to the lower limb

Participants will be included after clarification of inclusion and exclusion criteria by a clinical examination and after comprehensive written and oral information. All participants will have to sign a written informed consent in line with the Ethics Approval obtained from the Ethics Commission of the Canton Berne (Approval number: KEK-Nr. 158/12). Anthropometric data (gender, age, height, weight, shoe size and foot length) will be recorded according to guidelines of ‘Good Clinical Practice’ in subject specific Case Report Forms [40]. All subsequent data acquisition will also be documented in the Case Report Forms. This secures quality control of stored data and ensures that every single data item can be tracked down to its origin.

### Randomisation

Randomisation for group allocation to Foot Orthoses Only (FOO), Foot Orthoses with Eccentrics (FOE) or Sham Foot Orthoses (FOS) will take place with the online tool www.randomization.com (no blocking or stratification will be used). The biomechanical testing (standing, walking and walking down a stairway) will be administered in a fixed sequence since standing posture serves as calibration for dynamic measurements. Group allocation will be conducted using opaque sealed envelopes (i.e., concealed allocation). The allocation list will be stored separately and measurement personnel and data analysing personnel will not be involved in group allocation. Medical doctors, responsible for recruitment and checking of eligibility, will also not be involved in group assignment.

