### Data analysis

Data will be transferred from Case Report Forms to Microsoft® Excel for Windows (current version) spread sheets and later processed by SPSS® (current version). Biomechanical data will be processed with the outlined software and final quantities will also be transferred to spreadsheets for statistical analysis.

Statistical analysis will be performed descriptively after plausibility control. First, testing of normal distribution (Shapiro-Wilk test) of data will be followed by the calculation of mean, standard deviation and 95 % confidence interval. Primary outcome measure (FFI total score) at measurement points 0, week 6 and week 12 will be analysed by 3x3 Analysis of Variance (ANOVA) with repeated measures identifying differences in the FFI across groups (FOO, FOE, FOS) and test sessions. This also applies for the secondary outcome measures (FFI pain subcategory, FFI disability subcategory and FFI activity limitation subcategory). The primary endpoint will be set at 12 weeks. Biomechanical data will be analysed descriptively. Pre-post comparisons of those tertiary outcome measures will also be performed where indicated after descriptive analysis by 2×2 repeated measures ANOVA (factor group and test day).

Sample size calculation has been based on the outlined protocol with three intervention groups and the same primary outcome as Kulig et al. [14, 15], where a sample size of *n* = 15 per group (total *N* = 45) was determined based on clinical observation, attrition rate and power analysis. Clinical observation suggested that there is moderate to high inter-subject variability with respect to pain, disability and function (patient’s perception). A drop-out rate of 20 % is assumed due to a long intervention period, increase or resolution of symptoms during the intervention, or a need for surgery requiring exit from the study. Power analysis was based on an alpha level of 0.05 and beta of 0.8 resulting in the proposed sample size of 45 [38].

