Based on this reported sample size with the same main outcome and design, an *à priori* calculation of the total sample size was performed leading to a group sample of *n* = 20 (total *N* = 60) according to the following assumptions (Software: G*Power3, [68, 69]: test family = F-tests, statistical test = repeated measures ANOVA, effect size = 0.2 (medium), alpha = 0.05, power = 0.82, number of groups = 3, number of measurements = 3, correlation among the repeated measures = 0.5, nonsphericity correction epsilon = 1 and dropouts *n* = 6).

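### Minor: allocation without blocking does not secure the planned 20 per group unless the list totals are fixed, which the article does not say

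*Protocol article*

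**What the plan says.** The Study design section describes three parallel groups. Under Study population, "A cohort of 60 participants will be recruited out of six state-wide foot surgery centres". The Randomisation section says that allocation uses an online tool and that "no blocking or stratification will be used". It continues: "Group allocation will be conducted using opaque sealed envelopes (i.e., concealed allocation". The list is stored separately, and neither the recruiting doctors nor the measurement and analysis staff take part in assignment. No allocation ratio is given, and nothing says whether the list contains a fixed number of places per arm.

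The Data analysis section reports an a priori calculation "leading to a group sample of *n* = 20 (total *N* = 60". Its inputs are "effect size = 0.2 (medium), alpha = 0.05, power = 0.82, number of groups = 3, number of measurements = 3" and "correlation among the repeated measures = 0.5, nonsphericity correction epsilon = 1 and dropouts *n* = 6". Nothing in the calculation allows for arms of unequal size.

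**The concern.** The calculation treats 20 per group as a fixed design quantity: 18 per group analysed once the 6 dropouts are shared equally. If each assignment is an independent draw, the arm sizes are random, and with only 60 people in three arms they vary noticeably.

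A small arm weakens two of the three pairwise comparisons, and dropout then comes out of an arm that is already short. The stated power of 0.82 leaves little to spare. An analysis plan cannot repair this, because arm sizes are settled at allocation.

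**Working it through.** **Inputs.** From the article: 60 participants, 3 groups, 20 per group, 6 dropouts (so 54 analysed), effect size f = 0.2, alpha = 0.05, 3 measurements, correlation 0.5, epsilon 1. Assumption: independent assignment with probability 1/3 per arm.

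**1. The plan's own power.** For the group-by-time interaction, the noncentrality is λ = f²·N·m/(1 − ρ) = 0.04 × 54 × 3/0.5 = 12.96. The degrees of freedom are (3 − 1)(3 − 1) = 4 and (54 − 3)(3 − 1) = 102. Power is 0.816, against the stated 0.82. Adding 6 dropouts gives 60, so the plan's figure is reproduced. The other two tests in the same design give 0.898 (within-subject factor) and 0.327 (between-group factor), so the interaction is the test that was powered.

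**2. Arm sizes under independent assignment of 60.** One arm's size has SD √(60 × 1/3 × 2/3) = 3.65. The chance of exact balance is 60!/(20!³ × 3⁶⁰) = 0.0136. Enumerating every possible split gives:

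| Event | Probability |
|---|---|
| Exactly 20/20/20 | 1.4% |
| All arms between 18 and 22 | 22.9% |
| Smallest arm 15 or fewer | 31.7% |
| Smallest arm 14 or fewer | 18.8% |
| Smallest arm 12 or fewer | 5.1% |
| One named arm 15 or fewer | 10.7% |
| Largest minus smallest 8 or more | 47.0% |

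The expected smallest arm is 16.3 and the expected largest 23.8.

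**3. Precision of pairwise contrasts.** Relative to 20 versus 20, with variance proportional to 2/20 = 0.10, a 15/22/23 split gives:
- 15 versus 22: (1/15 + 1/22)/0.10 = 1.12
- 15 versus 23: (1/15 + 1/23)/0.10 = 1.10
- 22 versus 23: (1/22 + 1/23)/0.10 = 0.89

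Two contrasts lose 10 to 12% and the third gains 11%. The mean of the three is 1.04.

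**4. Power under random splits of the 54 analysed.** Imbalance multiplies λ by the ratio of the weighted to the balanced between-group variance of the effects. Averaged over all splits, power is 0.804, against 0.816 in balance. This holds whether one arm differs from the other two or the three effects are evenly spaced.

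Single splits move it both ways. Take 13/20/21 with one arm differing from the other two:
- If the arm of 13 differs, the multiplier is (13/54)(41/54)/(2/9) = 0.823. Then λ = 10.66 and power is 0.725, a loss of about 9 points.
- If the arm of 21 differs, power is 0.844.

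An arm of 13 or fewer among 54 arises in 28.1% of splits. The full loss also requires that the short arm be the one that differs.

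**The case against.** The best defence is that the article does not state independent assignment. It describes a stored list and envelopes and plans 20 per group. One randomly ordered list of 20/20/20, with no blocks inside it, fits every sentence and would give exactly 20 per arm at completion. This stands as a limit on the point: the probabilities above are conditional. It does not dispose of the point, because a reader would ordinarily take the wording to mean simple randomisation, and nothing corrects that.

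Second, simple randomisation is valid, openly declared and the hardest scheme to predict, which has value when participants know their treatment. That is true. A reader might infer bias or an invalid design; the documents support neither. The low chance of exact balance also overstates the harm, since 19/20/21 fails that criterion at virtually no cost. The average power loss of about one point is the fairer summary.

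Third, a reader might infer that the plan should have stratified by stage of tendon dysfunction, since stages I and II are both eligible and stage is known before allocation. The article does not show that stage predicts change in the Foot Function Index, and the group-by-time test already removes stable level differences between arms. Chance imbalance is also easily overstated. If half the participants are stage II (an assumption) and arms have 20 each, some pair among the three arms differs by 25 points or more in 33% of trials, but a named pair does so in 15%. If 30% or 70% are stage II, the figures are 26% and 12%. Stratification remains a preference.

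**Conclusion.** The point holds as a minor one. As worded, the allocation method does not reliably deliver the group size on which the calculation rests. Assuming independent assignment with probability 1/3, exact balance occurs in 1.4% of trials and an arm of 15 or fewer in about 32%. The cost is one of efficiency: power of about 0.80 on average instead of 0.82, with a loss of about 9 points in an unfavourable split such as 13/20/21 where the short arm is the one that differs.

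It would go too far to call the trial underpowered on this ground. The average loss does not show that, and some splits raise power. If the list in fact has totals fixed at 20 each, the numerical concern disappears and only the wording needs correcting.

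**What to change.** Before enrolment, build the list so that arm sizes are controlled, in one of two ways:

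- **Fixed totals:** one random ordering of 60 places, 20 per arm. Arms are exactly 20 at completion. If recruitment stops early, they may still differ.
- **Permuted blocks of randomly varied size,** for example 6 and 9, known only to the list holder. A block of 9 holds 3 places per arm, so arms never differ by more than 3, even if the last block is incomplete. Blocks that sum to 60, such as four of 6 and four of 9 (24 + 36), end at 20/20/20.

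State the choice in the Randomisation section. If the list already has fixed totals, one added sentence saying so is enough.

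The cost is a new list and envelope set. The downside is slight predictability of late assignments: near the end of a fixed-total list, or at the end of a block. Opaque envelopes, a separately stored list and recruiters with no part in assignment already limit it. Stratification by stage may be added if the investigators want it, but this fix does not need it.

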### Blinding

Blinding of the intervention to the participants is not possible as participants will recognise the allocated therapy. The study personnel will refrain from explaining hypothetical effects of foot orthoses, eccentric exercise or sham foot orthoses. The measurement and data analysis personnel will be blinded to group allocation during data acquisition and data analysis. De-blinding will take place after statistical analysis has been completed.

### Procedure

After the clinical examination, participants will be forwarded to the study centre for further anamnestic (medical history) pre-tests. A 1st measurement appointment will then be finalised. Meanwhile, fabrication of the foot orthoses takes place. At the 1st measurement appointment, participants’ anthropometrics and static unloaded and loaded foot posture for characterisation will be assessed. Following this, the participants’ foot health status (using the Function Index FFI, German Version (or FFI-D) [41, 42]), functional impairment (using the Pain-Disability-Index PDI [43, 44]), and current pain perception (using a VAS [38]) will be assessed. Biomechanical measurements of standing posture, level walking and walking down stairs will then be taken. After biomechanical testing, a re-evaluation of pain assessment with a VAS will be conducted.

After the 1st measurement appointment, an intervention period will follow for 12 weeks. All participants will receive a guideline for load management during the intervention and an activity diary with accompanying assessments (FFI, PDI and VAS after 6 weeks). After the 12-week intervention period, a 2nd assessment of the patient’s foot health status (FFI), functional impairment (PDI) and current pain perception (VAS pre/post-test), as well as the biomechanical tests will follow. If symptoms persist at the end of this period, participants will be transferred to the initial foot surgery centre for further medical assessment and possible ongoing therapeutic care.

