#### Foot Orthoses Only (FOO)

Participants in this group will receive custom-made foot orthoses fabricated by the same orthopaedic technician (AR, Ortho-Team AG, Bern, Switzerland). Foot orthoses will be fabricated out of Ethylene Vinyl Acetate (EVA, shore 40) with a thickness at the base of approximately 4 mm. The foot will be cast in a three-dimensional foam box impression in the neutral position of the foot under partial weightbearing [46]. This neutral position is already a “corrected” position for patients with the mentioned pathology. The 3D foam box impression serves as the basis for implementing correcting elements in the foot orthoses via computer-aided design software (CAD). A medial longitudinal arch is provided for arch support and a bowl-shaped heel is integrated to promote rear foot stability. Finally, the foot orthoses will be fabricated out of an EVA block by means of computerised numerical control technology (CNC). A dynamic barefoot plantar pressure distribution to evaluate dynamic foot function during walking (foot progression angle, forefoot abduction and medial loading) and qualitative gait analysis will be performed to support decision making on the amount of medial arch posting [43]. A medial longitudinal arch support will increase pressure at the medial plantar surface [47, 48], which might lead to changes in afferent input triggering neuromuscular control [34]. A top layer of Alcantara will be glued on top of each orthosis (Table 1). All participants will wear the device throughout the 12-week intervention for a minimum of 80 % of weight-bearing tasks.

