#### Foot Orthoses Sham (FOS)

This group will receive individually customised (sham) foot orthoses out of the same material described above. The functional elements of the sham orthoses, like arch support or a bowl-shaped heel to promote rearfoot stability, are designed to assist with blinding of patients. The foot will also be cast in a three-dimensional foam box impression without “correcting” to a neutral position of the foot under partial weightbearing [46]. The sham orthoses will not receive correcting elements via computer-aided design software (CAD). The sham foot orthoses will also fabricated out of an EVA block by means of computerised numerical control (CNC) technology. Like the other orthoses, a layer out of Alcantara will be glued to the top of the sham orthoses. All participants will wear the device throughout the 12-week intervention for a minimum of 80 % of weight-bearing tasks. The participants in this group will also get an activity booklet to record possible accompanying activity.

All three groups will receive a phone call after one, four and eight weeks to check for compliance, uncertainties and questions (Fig. 1). If necessary, monitoring sessions for members of the FOE group with the physiotherapist will be organised every four weeks to control exercise execution and to implement training load adjustments [52]. Where participants experience obvious fitting problems, orthoses will be slightly modified as necessary to ensure comfort and shoe fit.

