### Outcome measures

#### Foot-Function-Index (FFI)

The evaluation of therapy efficacy will be conducted with the main outcome measure, the FFI, before and after the intervention. It will be administered before the biomechanical testing on the pre/post measurements. The FFI is recognised as a valid and reliable tool [53, 54]. It is also available and valid for German language use [41]. Furthermore, it has been used already to evaluate PTTD patients with pes planovalgus associated complaints and is considered to be an excellent tool in this circumstance [14, 15]. The overall (i.e., total) FFI score will be analysed as the primary outcome measure. The subscales of the FFI in the dimensions pain, disability and activity limitation will be analysed separately as secondary outcome measures.

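### As described, orthoses are made before the first FFI and differ between active and sham, so the self-reported baseline of the primary analysis is taken after allocation, with no stated safeguard

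*Protocol article*

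**What the plan says.** All references are to the protocol article.

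- **Procedure.** After the clinical examination and the pre-tests at the study centre, the text continues: "A 1st measurement appointment will then be finalised". The next sentence is: "Meanwhile, fabrication of the foot orthoses takes place". The 1st measurement appointment starts with anthropometrics and foot posture. FFI, PDI and VAS come next, then the biomechanical tests. "After the 1st measurement appointment, an intervention period will follow for 12 weeks".
- **Foot-Function-Index (FFI).** On its timing: "It will be administered before the biomechanical testing on the pre/post measurements".
- **Foot Orthoses Only (FOO).** "The foot will be cast in a three-dimensional foam box impression in the neutral position of the foot under partial weightbearing". Correcting elements are then added in the CAD step. Under Foot Orthoses and Eccentrics (FOE), that group receives the same device.
- **Foot Orthoses Sham (FOS).** The impression is taken without bringing the foot to neutral, and the CAD step adds no correction. The same section says that the sham's functional features are there to help blind patients.
- **Randomisation.** One allocation to three arms by opaque sealed envelope. No time point is given.
- **Blinding.** Participants cannot be blinded, because they will realise which therapy they have. Measurement and analysis staff are blinded.
- **Interventions.** Instructions on the assigned therapy follow allocation. They are not tied to completion of baseline.
- **Data analysis.** FFI total at time 0, week 6 and week 12 enters a 3×3 repeated-measures ANOVA, with week 12 as the primary endpoint.

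**The concern.** A baseline is safe from influence by the assigned arm if it is recorded before anyone knows that arm. Here a device that depends on the arm is produced before the first questionnaire, so the arm has to be known to someone by then. FFI and PDI are self-reported, so blinding the measurement staff does not protect them. If participants know or sense their arm when they fill in the first FFI, expectation or disappointment can move that score. Because time 0 is one of the three outcome levels in the ANOVA, such a movement would appear as part of the group-by-time effect.

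A second consequence is loss of data. A participant who is allocated but leaves before the 1st appointment contributes no FFI at any time and cannot be analysed as randomised with observed data.

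**Working it through.** **Order of events**

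1. Procedure places fabrication between the pre-tests and the 1st measurement appointment.
2. Procedure places the first FFI at that appointment, so fabrication precedes the first FFI.
3. The FOO and FOS sections differ at the impression (neutral versus uncorrected) and again at the CAD step (correction versus none). Fabrication as described cannot begin without knowing active or sham.
4. From 1 to 3, at least active versus sham is known before the first FFI.
5. FOO and FOE share one orthosis, so fabrication alone does not separate these two. Randomisation describes a single three-arm allocation, however, and Interventions dates instructions from allocation. Nothing in the text delays an FOE participant's learning of the exercise arm until baseline is done.

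The inference would fail if both devices were made for everyone, or if the arm-specific steps followed the baseline visit. The text says neither.

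**Size**

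Inputs from Data analysis: f = 0.2, alpha = 0.05, 3 groups, m = 3 measurements, rho = 0.5, epsilon = 1, and 60 − 6 dropouts = 54 evaluable (18 per arm).

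*The plan's own figure.* For the group-by-time interaction, λ = f²·N·m/(1 − rho) = 0.04 × 54 × 3 / 0.5 = 12.96, with df 4 and (54 − 3) × 2 = 102. Power is 0.816 against 0.82 stated, so the formula matches the planned test. The within-factor version gives 0.898 and the between-factor version 0.327.

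*Effect of a baseline shift.* Assume no treatment effect and a shift of b SD in one arm at time 0 only. In a simple two-arm contrast of change, the later difference minus the baseline difference is 0 − b = −b, so the shift passes through in full. In the 3×3 layout, the interaction sum of squares over the nine cells is b² × (2/3) × (2/3) = 4b²/9. The mean square over cells is 4b²/81, so f = 2b/9 and λ = 54 × 3 × (4b²/81) / 0.5 = 16b².

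| Assumed shift b (SD) | f | λ | Rejection rate of nominal 5% test |
|---|---|---|---|
| 0 | 0 | 0 | 5.0% |
| 0.1 | 0.022 | 0.16 | 5.8% |
| 0.2 | 0.044 | 0.64 | 8.2% |
| 0.3 | 0.067 | 1.44 | 12.9% |
| 0.5 | 0.111 | 4.00 | 30.6% |

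The document gives no value for b and no direction. The table shows only how sensitive the planned test is. Losses between allocation and the 1st appointment cannot be quantified from the document.

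**The case against.** The strongest reply has four parts.

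- **The order is not stated.** No section says when the envelope is opened, and the flow chart, which is not shown, might. Procedure is also incomplete: it does not place consent, casting, allocation, or the plantar-pressure and gait analysis used to set the arch posting. An article may leave such detail to the full protocol. This stands as a caution. It does not remove the point, because the article itself fixes an order in which an arm-specific device precedes the first FFI.
- **Bias needs the participant, not just the technician, to know.** A reader might infer that participants know their arm at the first FFI. The document does not say so. The sham is individually cast in a foam box, has the same material and top layer, and carries features meant to aid blinding. Staff do not explain expected effects, and the intervention period starts after the 1st appointment. The statement that participants will recognise their therapy has no date. This part stands: bias is possible and is not shown. Even so, the Blinding and FOS sections pull in opposite directions, and neither says that awareness is withheld until baseline is complete.
- **Not every contrast is exposed in the same way.** A reader might infer that fabrication reveals all three arms. It does not, since FOO and FOE wear the same orthosis. That contrast is exposed only through the undated instructions.
- **Moving the VAS would do harm.** It is defined as a pair of readings before and after the biomechanical test. This stands, and the VAS should stay where it is.

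**Conclusion.** The point holds as a weakness in the stated sequence. Read together, Procedure and the three intervention sections put the self-reported baseline after at least the active-versus-sham allocation, in a trial that says participants cannot be blinded. That baseline is time 0 of the primary analysis. The conclusion rests on the described order being followed and on the missing flow chart not contradicting it.

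A reader might go further and conclude that the baseline is biased or the primary result invalid. The documents do not support that, because they do not show what participants know at the first FFI. Under assumed one-arm shifts of 0.1 to 0.2 SD the false-positive rate rises from 5% to about 6% to 8%. Larger shifts would matter more, but nothing in the document points to a particular value. Sample size is unaffected. The change is worth making because it is cheap and closes the route.

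**What to change.** **Preferred.** Take the baseline FFI and PDI at the existing study-centre pre-test visit, before the envelope is opened and before arm-specific casting, and use them as time 0. State the order: consent, baseline questionnaires, allocation, casting. Keep the VAS and the biomechanical baseline at the 1st measurement appointment, and amend the sentences on FFI and PDI timing to match.

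**Minimum.** State when the envelope is opened. Specify that participants are not told their arm, and receive no arm-specific instructions, until the first FFI, the first PDI and the VAS before the biomechanical test are complete. Under the preferred option this rule is still useful for the VAS.

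**Cost.** The preferred option moves two questionnaires to a visit that already takes place. Its downside is that the FFI and PDI baseline then precedes the start of treatment by the fabrication interval, which the document does not give. The minimum option avoids that gap, but participants lost between allocation and the 1st appointment would still have no FFI.
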